# FORESEEABLE RISKS AND DISCOMFORTS

Provide a brief description of any foreseeable risks and discomforts to subjects. Include those related to drugs/devices/procedures being studied and/or administered/performed solely for research purposes. In addition, include psychosocial risks, and risks related to privacy and confidentiality. When applicable, describe risks to a developing fetus or nursing infant.

The risk for this study is minimal. The study consists of wearing an activity monitor that wirelessly uploads activity and sleep data to a website . Every resident who participates in the Be Fit program has 2 physical assessments and blood tests and fills out 2 surveys. If a resident is participating in the research study, their data will be included in the research database. Psychosocial and privacy risks are also estimated to be minimal. Confidentiality will be ensured by de-identifying subjects’ data with study identification numbers.

All study subjects will receive an activity monitor. This device does not pose any medical risk and does not diagnosis any medical conditions or illnesses. Wearing the activity monitor may cause minimal discomfort. The device is small, weighing only a few ounces, and can be easily worn on the torso by attaching it to a belt or waistband, pants, a shirt, or an undergarment.

**EXPECTED BENEFITS**

# Describe both the expected benefits to individual subjects participating in the research and the importance of the knowledge that may reasonably be expected to result from the study. Provide a brief, realistic summary of potential benefits to subjects, for example, “It is hoped that the treatment will result in a partial reduction in tumor size in at least 25% of the enrolled subjects.” Indicate how the results of the study will benefit future patients with the disease/condition being studied and/or society, e.g., through increased knowledge of human physiology or behavior, improved safety, or technological advances.

Study participants may not receive any direct benefit from being in the research study. It is hoped that participation in the intervention will help subjects increase their activity levels and therefore improve or prevent clinical risk factors that are associated with disease.

The results of this research may provide better understanding of how to help medical residents and other employees increase their activity levels, and if these changes are associated with improved sleeping habits and prevention of weight gain. The results could also inform other institutions about the benefits of establishing similar programs.

**EQUITABLE SELECTION OF SUBJECTS**

The risks and benefits of the research must be fairly distributed among the populations that stand to benefit from it. No group of persons, for example, men, women, pregnant women, children, and minorities, should be categorically excluded from the research without a good scientific or ethical reason to do so. Please provide the basis for concluding that the study population is representative of the population that stands to potentially benefit from this research.

All MGH Medicine residents are eligible to participate in the Be Fit program. Children will be excluded because medicine residents are typically at least 24 years old. Otherwise, no group of men, women, pregnant women, or minorities will be excluded from the study.

When people who do not speak English are excluded from participation in the research, provide the scientific rationale for doing so. Individuals who do not speak English should not be denied participation in research simply because it is inconvenient to translate the consent form in different languages and to have an interpreter present.

All MGH medicine residents are proficient in English.

For guidance, refer to the following Partners policy:

Obtaining and Documenting Informed Consent of Subjects who do not Speak English

[**http://healthcare.partners.org/phsirb/nonengco.htm**](http://healthcare.partners.org/phsirb/nonengco.htm)

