### SPECIFIC AIMS

Concisely state the objectives of the study and the hypothesis being tested.

The main objective of this study is to test an intervention to increase the physical activity of medical residents, an employee population with little time for exercise. Specifically, the aims of this study are:

1. To determine if providing medical residents with an activity device that measures steps, distance, and calories burned and tracks this information over time on a website increases residents’ physical activity levels as measured by number of steps per day compared to a control group using a blinded activity device (no feedback).
2. To determine if an unblinded team competition using the activity device directly following the randomized phase increases residents’ activity level compared to baseline.
3. To determine if activity level is associated with change in weight during the residency year.
4. To determine if the average hours of sleep per week is associated with changes in weight and with activity level.

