Team competition phase: Immediately following the randomization phase, all study participants will be unblinded and able to view the Fitbit feedback both on the device and on the website. The control group will be given a password to be able to log on to their personalized Fitbit website. The residents will be divided into 3 teams based on their class: interns, juniors, or seniors. The teams will compete on the average number of steps per week. The team standings will be displayed on the Fitbit website that will be viewed by each study subject. Teams will compete for 6 weeks.

Data to be collected:

Physical assessment*:* All residents who enroll in the Be Fit program will be asked to attend a physical assessment at baseline (between July and November 2010) and at the end (May 2011). All physical assessments will be conducted prior to 10 o’clock in the morning. During these visits, study staff collect weight, height, waist measurements, body fat, blood pressure, and heart rate.

Fasting blood test*:* During each physical assessment, residents enrolled in Be Fit undergo a fasting blood test for lipids. Residents are asked not to have anything to eat or drink after midnight the day before the test.

Survey: All residents enrolled in Be Fit will complete a survey at baseline and at the end of the program. The survey collects information on smoking history, physical activity, and nutritional habits. Age, sex, race/ethnicity, marital status, education level, and care for dependents at home (children, disabled/ill spouse, parent, or child) will be recorded on the survey. The survey also includes a scale that measures psychological stress, called the Schwartz Outcome Scale-10 © (SOS-10 TM). The SOS-10 is a 10 item survey tool to determine a person’s distress level. It is not a diagnostic instrument and cannot be used for making psychiatric diagnoses. The scores range from 0 to 60. Higher scores reflect better psychological health and lower scores indicate emotional distress and lower levels of psychological health. There is a cut off score of 43, and a change of 8 points or greater are a reliable indicator that a person’s psychological status has either improved or deteriorated.

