Data from Fitbit website: Only residents who enroll in the research study will be given a Fitbit activity device. All activity data and sleep data recorded during the study period will be collected. The Fitbit website provides individual data on the number of steps per day, the number of calories burned per day, and the number of hours slept per 24 hour period. This data will be collected from all study subjects during both the randomized phase and the team competition phase of the study.

Study endpoints:

Primary endpoint: The primary endpoint of the study will be average activity level per resident as measured by number of steps per day. In the randomized phase, the average number of steps per day in the intervention group (Fitbit + feedback) will be compared to the average number of steps per day in the control group (Fitbit without feedback). In the second phase, we will compare the change in the average number of steps for each participant compared to their own baseline number of steps from the first phase.

Secondary endpoints: Secondary endpoints will be change in weight during the study period and number of hours of sleep per 24 hour period for each resident. Survey data will be used to examine reported changes in physical activity levels, nutritional habits, and sleep habits. The survey data will also provide data from the SOS-10 scale on change in psychological stress.

Statistical methods:

In the randomized phase, the average number of steps per day in the intervention group (Fitbit + feedback) will be compared to the average number of steps per day in the control group (Fitbit without feedback) using a two-sample t test or a Wilcoxon rank sum test whichever is more appropriate. To determine whether team competition increases activity level, the primary and secondary endpoints from the second phase will be compared to results from the first phase using paired t-tests. The changes in primary and secondary endpoints during study periods will be compared between the two randomization groups using a two-sample t test, and compared among the residency year groups using an analysis of variance approach. To determine if the average hours of sleep per week is associated with changes during study period, Pearson or Spearman correlation coefficients will be used to summarize the correlation between sleep time and change in weight/number of steps.

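### Pregnant residents may be enrolled and weight change is an outcome, but pregnancy and recent delivery are not among the listed data items, so affected weights could not be identified

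*Protocol*

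**What the plan says.** Eligibility (Protocol, Equitable Selection of Subjects): "Otherwise, no group of men, women, pregnant women, or minorities will be excluded from the study". The only withdrawal reasons given under Research Design and Methods are leaving employment at the hospital and the subject's own request.

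Outcomes: "Secondary endpoints will be change in weight during the study period and number of hours of sleep per 24 hour period for each resident". Aim 3 is "To determine if activity level is associated with change in weight during the residency year". Aim 4 is "To determine if the average hours of sleep per week is associated with changes in weight and with activity level".

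Timing: the physical assessment takes place at "baseline (between July and November 2010) and at the end (May 2011"). These are the only two weighings scheduled.

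Data collected: "During these visits, study staff collect weight, height, waist measurements, body fat, blood pressure, and heart rate". The blood test is for lipids. On the questionnaire, "The survey collects information on smoking history, physical activity, and nutritional habits". It also records "Age, sex, race/ethnicity, marital status, education level, and care for dependents at home", along with a psychological distress scale, and the parameters section adds sleep. The activity monitor supplies steps, calories and sleep. Pregnancy and delivery do not appear in any of these lists.

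Analysis (Statistical methods): changes in the endpoints are compared between arms by t-test and between class years by analysis of variance. Sleep is related to weight change and to steps by a Pearson or Spearman correlation. No covariate or exclusion is stated for the weight analyses.

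**The concern.** The two weighings are about 6 to 10 months apart, long enough to contain most of a pregnancy, or a delivery. For a resident in either situation, the change in weight, BMI, waist or body fat is not the quantity the endpoint is meant to capture. A pregnancy under way in May shows as a gain. A delivery between the weighings can show as a loss.

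Two consequences follow. Large changes of either sign widen the spread of weight change and so cost precision in the arm and class-year comparisons. Also, if pregnancy lowers steps or alters sleep, a few residents become influential points in the correlations. A gain combined with fewer steps has the sign one would expect under Aim 3, so a spurious result would be easy to accept.

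This cannot simply be left to a statistical analysis plan. Such a plan can set values aside only if the status that identifies them was collected, and what is collected is fixed in the protocol.

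**Working it through.** **The plan's own figure.** The protocol computes only the power for steps: 50 per group, difference 1200, SD 2000, two-sided 0.05. The noncentrality is 1200/(2000 × √(2/50)) = 1200/400 = 3.0 on 98 degrees of freedom, which gives 84.4% against the stated 84%. It reproduces and is not in dispute. The protocol gives no figure for weight.

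**Interval.** July to May is 10 months and November to May is 6 months.

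**Inputs for the illustration.** From the protocol: about 100 residents and a step SD of 2000. Assumed, not in the documents: weight-change SD 3 kg, no true association, k pregnant residents gaining 8 or 12 kg, and 0 to 2000 fewer steps a day.

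**Spread of weight change.** With a fraction p = k/100 shifted by g kg, the variance is 3² + p(1 − p)g². For k = 3, p(1 − p) = 0.03 × 0.97 = 0.0291.
- g = 8: 9 + 0.0291 × 64 = 10.86, SD 3.30 kg, variance +21%. In precision this equals losing 1 − 9/10.86 = 17% of the sample.
- g = 12: 9 + 0.0291 × 144 = 13.19, SD 3.63 kg, variance +47%, equal to losing 1 − 9/13.19 = 32%.

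**Spurious correlation (Pearson).** With a step shift d, the covariance is p(1 − p)gd and the step variance is 2000² + p(1 − p)d². For k = 3 and d = −2000, the step SD is √(4,000,000 + 116,400) = 2029.
- g = 8: −465.6/(3.30 × 2029) = −0.07.
- g = 12: −698.4/(3.63 × 2029) = −0.095.
- For k = 1, g = 12: −237.6/(3.23 × 2010) = −0.04.

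**Rejection rate of a 5% test of zero steps-weight correlation** (simulation, 4000 runs per row):

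| Pregnant residents | Gain (kg) | Step change | Pearson | Spearman |
|---|---|---|---|---|
| 1 | 12 | −2000 | 6.2% | 5.7% |
| 2 | 12 | −2000 | 10.6% | 6.3% |
| 3 | 8 | −1000 | 6.5% | 5.2% |
| 3 | 8 | −2000 | 11.3% | 6.6% |
| 3 | 12 | 0 | 5.0% | 4.6% |
| 3 | 12 | −1000 | 7.7% | 5.8% |
| 3 | 12 | −2000 | 14.8% | 7.0% |
| 5 | 12 | −2000 | 29.5% | 10.4% |

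Repeat runs of the row with 3 residents, 12 kg and −2000 steps gave Pearson rates of 15 to 16%. The sleep correlations were not simulated. The same mechanism applies to them if pregnancy changes sleep.

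**The case against.** A reader might infer that pregnant residents are in the study, that pregnancy is never recorded, and that gestational gain will therefore produce a false activity-weight link. The documents do not support that much. The eligibility sentence answers a form prompt that itself names pregnant women. It says only that they are not excluded, and no expected number is given. The questionnaire is described but not shown, so the supportable statement is that pregnancy is not among the listed items. Care for dependents, asked at both surveys, might hint at a delivery, although it neither dates one nor shows a current pregnancy.

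The size is also conditional. The higher rejection rates need several pregnant residents, a large gain, a step reduction of a full SD, and Pearson. The protocol also allows Spearman, which a few extreme values affect much less. Its correlation sentence concerns sleep. No method is named for Aim 3, so the steps-weight calculation illustrates an analysis the protocol implies but does not specify.

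The affected analyses are secondary and not powered, and exclusion rules are commonly left to the analysis plan. All of this stands as a limit on size and certainty. It does not remove the gap, because an analysis plan cannot act on a status that was not collected.

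**Conclusion.** The point holds as a possibility that the listed data would not allow anyone to detect or correct. It concerns the secondary weight endpoint, the related body measures, and the weight parts of Aims 3 and 4. The primary step comparison is not affected. Randomisation leaves the between-arm weight comparison unbiased in expectation, so there the loss is of precision only.

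Under the stated assumptions, three pregnant residents would cost the weight comparisons the equivalent of about 17 to 32% of the sample. They would raise the false-positive rate of a steps-weight correlation to about 11-16% (Pearson) or 6-7% (Spearman), and only if they also walked about 2000 fewer steps a day. With one such resident, or with no change in steps, that rate stays near 5-6%. This is a cheap improvement worth making, and it does not threaten the trial's main conclusion.

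**What to change.** Keep pregnant residents eligible and in all step analyses. Add one yes/no item to the baseline and May surveys: currently pregnant, or delivered since or shortly before the baseline assessment. State that residents answering yes at either time are excluded from the analyses of change in weight, BMI, waist and body fat, and from the correlations of these with steps and sleep. Report an all-participant sensitivity analysis alongside, since part of the exclusion depends on status after randomisation.

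The cost is one survey item and one analysis sentence. A few residents drop out of these secondary analyses. The study also holds one more sensitive item about employees, which should be covered by the existing rules under Privacy and Confidentiality.

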**RECRUITMENT PROCEDURES**

Explain in detail the specific methodology that will be used to recruit subjects. Specifically address how, when, where and by whom subjects will be identified and approached about participation. Include any specific recruitment methods used to enhance recruitment of women and minorities.

Every Medicine resident rotates through a 4 week ambulatory block between July and November 2010. During this ambulatory block, each group of approximately 34 residents will be introduced to the Be Fit program and to the research study during a 1 hour session as part of their ambulatory block lecture series. If a resident chooses to participate in the Be Fit program, he or she will be asked to participate in the research study.

Provide details of remuneration, when applicable. Even when subjects may derive medical benefit from participation, it is often the case that extra hospital visits, meals at the hospital, parking fees or other inconveniences will result in additional out-of-pocket expenses related to study participation. Investigators may wish to consider providing reimbursement for such expenses when funding is available

To increase compliance with wearing the device on a regular basis, we will offer a small gift certificate at the hospital coffee shop as an incentive. All residents who wear the device regularly will be eligible each week to be entered into a raffle for the gift certificate. At the end of each week, we will calculate the number of days each resident has worn their Fitbit. All residents who have worn their Fitbit for 5 of the previous 7 days will be put into a raffle to win a $10 gift certificate for Coffee Central at MGH. The winner each week will be announced in the weekly email to all the study participants. We will conduct this raffle once a week for the entire 12 week study period.

At the end of the study, If the participant wears the Fitbit activity device for 75% of the intervention period (12 weeks), the study participant will be allowed to keep the device (retail value of $99.00) for their own personal use.

For guidance, refer to the following Partners policies:

Recruitment of Research Subjects

[**http://healthcare.partners.org/phsirb/recruit.htm**](http://healthcare.partners.org/phsirb/recruit.htm)

Guidelines for Advertisements for Recruiting Subjects

[**http://healthcare.partners.org/phsirb/advert.htm**](http://healthcare.partners.org/phsirb/advert.htm)

Remuneration for Research Subjects

[**http://healthcare.partners.org/phsirb/remun.htm**](http://healthcare.partners.org/phsirb/remun.htm)

#### CONSENT PROCEDURES

Explain in detail how, when, where, and by whom consent is obtained, and the timing of consent (i.e., how long subjects will be given to consider participation). For most studies involving more than minimal risk and all studies involving investigational drugs/devices, a licensed physician investigator must obtain informed consent. When subjects are to be enrolled from among the investigators’ own patients, describe how the potential for coercion will be avoided.

The PI will review the consent form during the 1 hour ambulatory block lecture with all the residents in the room. There will be 5 different 1 hour sessions with approximately 34 residents in attendance at each session. If the PI is not available for one of these sessions, a member of the research staff will review the consent form. Residents will be given the consent form to take home with them if they would like more time to read it over and will be given the opportunity to ask questions about the study. If a resident is not able to attend the 1 hour session, the PI or another study staff member will review the consent form with the resident individually. In order to participate in the research study, a resident must sign the consent form prior to the end of November 2010.

NOTE: When subjects are unable to give consent due to age (minors) or impaired decision-making capacity, complete the forms for Research Involving Children as Subjects of Research and/or Research Involving Individuals with Impaired Decision-making Capacity, available on the New Submissions page on the PHRC website:

[**http://healthcare.partners.org/phsirb/newapp.htm#Newapp**](http://healthcare.partners.org/phsirb/newapp.htm#Newapp)

For guidance, refer to the following Partners policy:

Informed Consent of Research Subjects

[**http://healthcare.partners.org/phsirb/infcons.htm**](http://healthcare.partners.org/phsirb/infcons.htm)

## DATA AND SAFETY MONITORING

Describe the plan for monitoring the data to ensure the safety of subjects. The plan should include a brief description of (1) the safety and/or efficacy data that will be reviewed; (2) the planned frequency of review; and (3) who will be responsible for this review and for determining whether the research should be altered or stopped. Include a brief description of any stopping rules for the study, when appropriate. Depending upon the risk, size and complexity of the study, the investigator, an expert group, an independent Data and Safety Monitoring Board (DSMB) or others might be assigned primary responsibility for this monitoring activity.

NOTE: Regardless of data and safety monitoring plans by the sponsor or others, the principal investigator is ultimately responsible for protecting the rights, safety, and welfare of subjects under his/her care.

This research study utilizes a minimal risk intervention. We do not expect adverse effects or safety concerns, nor do we anticipate the need for the Data Safety Monitoring Board to review this application.

Describe the plan to be followed by the Principal Investigator/study staff for review of adverse events experienced by subjects under his/her care, and when applicable, for review of sponsor safety reports and DSMB reports. Describe the plan for reporting adverse events to the sponsor and the Partners’ IRB and, when applicable, for submitting sponsor safety reports and DSMB reports to the Partners’ IRBs. When the investigator is also the sponsor of the IND/IDE, include the plan for reporting of adverse events to the FDA and, when applicable, to investigators at other sites.

NOTE: In addition to the adverse event reporting requirements of the sponsor, the principal investigator must follow the Partners Human Research Committee guidelines for Adverse Event Reporting

The PI will review all blood test results obtained from Be Fit participants to screen for abnormalities. She will review any adverse events or subject complaints, including any breech of confidentiality or privacy, and these will be reported to the Partners IRB in the annual continuing review. Any serious adverse events will be reported to the Partners’ IRB within 24 hours.

